### Quality control

This study will use a randomized control design. The randomization protocol will be carried out by the management team of the study who do not participate in the project to ensure the biases involved in the random allocation and control.This study will strictly limit the inclusion criteria and formulate clear inclusion and exclusion criteria to control biases.This study will use a blind method to ensure the reliability of the research results. Outcome evaluators and statistical analysts will all be blind to the randomization sequence and treatment allocation.During the study, we will use sEMG to avoid bias due to its objectivity and use MRI to view the morphological changes of the facial nerve from a more objective perspective.

### Quality assurance

Before the launch of the study, we will conduct a unified training for the participants involved in the implementation. Key training will be carried out on the project implementation plan and standard operation procedures (SOPs), so that each clinical researcher will be familiar with the research process and specific implementation rules which ensures the reliability of clinical research conclusions. Furthermore, we will also explain the operation method of acupuncture at the Yifeng (SJ17) acupoint and the Tinghui (GB2) acupoint.

### Data collection and management

Paper CRFs will be used to record all the first-hand clinical trial data of subjects. Researchers should ensure recording of the data is timely, complete, accurate, and true.

During the trial, a monthly data inspection will be needed. Researchers will follow the rule of confidentiality for the trial. The data obtained from the completed CRF is recorded into the database established by Microsoft Excel for data management. After the implementation of the statistical process, the content of the CRF will no longer be modified further. After obtaining the primary data which will be kept for 3 years, non-research team members will not be allowed to browse and borrow the data, outcomes, and analyses to the relevant parties, including the fund regulator, trial participants, trial registries, and journals.

### Plans to promote participant retention and complete follow-up

Participants will be reminded by the study investigators on every consultation time and will received notifications using the phone call and online instant messaging application “WeChat.”

The study team will educate the subjects about the development trend of disease when they enrolled for the study. Furthermore, the study team will provide acupuncture treatment and oral medicine for free. And to ensure that the treatments will be administered consistently, the acupuncturists which will be assigned have at least 5 years of clinical experience in acupuncture practice.

### Data monitoring and auditing

There is no additional data monitoring committee. Instead, the study investigators will monitor the survey data in the database on a regular basis for any issues. If there are any issues, they will be discussed at the weekly study team meetings. Once any issues are detected by study investigators, those issues will be reported strictly to the principal investigators immediately, who will then escalate them to the Ethics Committee of the First Teaching Hospital of Tianjin University of TCM when appropriate.

### Informed consent

Before conducting a conversation with the subject, the researcher will explain the entire content of the informed consent form to the subject in a simple and understandable language. The content will include the purpose of the test, the test process, the possible benefits and risks, and the rights and obligations of the subjects. After the subjects learned the details, they decided to voluntarily participate in this clinical trial and voluntarily sign the “informed consent.” They will be having the right to withdraw at any given time and at any stage of the trial without discrimination or retaliation. This trial will comply with the rights and obligations of the subjects as stipulated in the Declaration of Helsinki.

### Post-trial care

This study will not provide any post-trial care.

### Protocol amendments

Participants may request to discontinue participation in the study at any time. In addition, if there are complications that affect the patient’s condition during the treatment, we will modify the intervention.

If the protocol changes during the implementation of the study, researchers will communicate the important protocol modifications (e.g., changes to eligibility criteria), and paper CRFs will be used to record all the first-hand clinical trial data of the subjects. Researchers should ensure recording of the data is timely, complete, accurate, and true.

### Confidentiality

This study follows the ethical principles set out in the “Helsinki Declaration” and the various laws and regulations related to clinical research in China. During the study, patients will receive treatments such as electroacupuncture. In addition, patients will receive free sEMG examination, MRI examination, and various evaluation tests. There is a minor chance of fainting, bleeding, hematoma, or infection during the study. If such situations appeared, we will treat the patient appropriately and record it in time**.**

## Discussion

Bell’s palsy, is the most frequently encountered type of peripheral facial palsy. It is an acute and self-limiting form of inferior motor neuron palsy. However, some part of patients cannot recover to the condition before the illness. The only prognostic factor of IFP is the state of the facial nerve 1 week after the onset [35], and the treatment in the acute phase of the disease largely determines the fate of FN and the recovery of facial function. Therefore, finding an effective treatment 1 week after the onset of illness is essential for an optimistic recovery. Previous studies have proved that steroids can relieve facial nerve edema. However, due to the compression state formed in the facial nerve canal in the acute phase, local blood circulation can be impaired. This may prevent oral steroids from reaching effective blood concentration in the facial nerve canal lesion, thereby affecting the efficacy and becoming a bottleneck in treatment. Stimulating the facial nerve canal through electroacupuncture locally may promote blood circulation in the facial nerve canal and relieve inflammatory edema. At the same time, improvement in the local microcirculation creates favorable conditions for the drug to reach effective blood concentration.

Worldwide, IFP is considered to be one of the most suitable indications for acupuncture treatment. Acupuncture has become the main treatment for IFP and exhibited significant effect according to the results of preliminary systematic evaluation and clinical studies. Electroacupuncture therapy is a kind of stimulation which directly acts on the target nerve through a combination of local acupuncture stimulation and electrical stimulation. Whether electroacupuncture can be used in the acute phase is still a subject of controversy. However, in the present study, the implementation of electracupuncture was scientific, detailed and innovative. Combining the theories of traditional acupuncture with modern anatomy, we select the Yifeng (SJ17) and Tinghui (GB2) electroacupuncture points to intervene in the acute phase of IFP; it will act directly around the target nerve.

According to the modern anatomical body surface projection positioning, Yifeng (SJ17) is close to the stylomastoid foramen (SMF), where the junction of the intracranial and intratemporal of the facial nerve is present. Tinghui (GB2) is close to the arborization of the extratemporal facial nerve which typically begins within the substance of the parotid gland [11]. The above two acupuncture points are markedly close to the facial nerve. Acupuncturing these two acupoints to a certain depth can directly stimulate the area around the FN. Stimulation frequency is one of the important parameters of electroacupuncture. Choosing different frequencies has completely different positions and effects. In the acute phase of the present study, the dilatational wave with a frequency of 2/10 Hz of electroacupuncture is used, which can relax and contract muscles rhythmically, accelerate blood circulation and lymphatic circulation, regulate the nutrient metabolism of tissues, and eliminate inflammation and edema [36]. Stimulating at the neuromuscular junction induced by acupuncture can lead to afferent sensory networks and activate the paraventricular nucleus of the hypothalamus to secrete vasopressin, corticotrophin-releasing hormone, and then, adrenocorticotrophic hormone (ACTH) is released into the bloodstream. ACTH then activates the zona fasciculate of the cortex of the adrenal glands to release glucocorticoids [37–39]. Previous studies have shown that [40], at the later stage of treatment, the number of Nissl bodies which represent the survival of neurons has returned to pre-injury level. Further, on the 14th and 21st days, more myelinated axons and fewer inflammatory cells were found in the electropuncture group. However, in the recovery phase, the sparse wave with a frequency of 20 Hz of electroacupuncture is used. Continuous stimulation at this phase will cause repeated local muscle contractions, which is helpful for local blood circulation of the face. Studies have shown that electroacupuncture invention can also help repair damaged nerves and promote their recovery of the nerve recovery phase [41].

In the design of clinical trials, the selection of appropriate outcome indicators is critical to evaluate the clinical efficacy. Nowadays, most evaluation methods related to facial nerve function of patients mostly rely on neurological function scales and electrophysiological data and cannot easily observe changes in symptoms and condition. Hence, in the present study, we not only used a series of evaluation scales certified by international guidelines, but also used more intuitive detection technologies such as surface electromyography and MRI, which can evaluate the clinical efficacy before and after the treatment. Surface electromyography can more objectively reflect the recovery of the patient’s facial muscle function, whereas MRI can more directly reflect the recovery of facial nerve edema from the morphology. Moreover, we used NRS to evaluate the degree of pain behind or around the ear, although this symptom did not observe in all the patients. However, according to the epidemiological survey on IFP in the early years, the incidence of pain behind or around the ear is 63% [42], which often affects the recovery of the condition. Therefore, we conducted a statistical analysis and analyzed the degree and duration of pain.

However, this study also has few limitations. First, due to the particularity of acupuncture, we could not blind acupuncturists and patients; however, only evaluators and statisticians were blinded as much as possible. Second, the time interval between follow-up visits was too long, with no other follow-up points set due to the limited research funding and time. Part of the reason was related to the patient’s complex compliance problem. Most patients ended the cycle of follow-up observation in advance after meeting the remarkable improvement of acupuncture treatment. Nevertheless, this research will provide reliable evidence of efficacy and safety for the clinical treatment related to IFP.

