#### NRS

The NRS uses numbers 0–10 to represent the degree of pain. The basic method is to divide a straight line into 10 equal parts, and the two ends of the line are numbered “0” and “10,” whereas 0 means no pain, 10 means severe pain which is unbearable, 1–3 means mild pain, 4–6 means moderate pain, and 7–9 means severe pain. The measurements will be performed within the baseline and day 10 after onset.

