### Statistical analysis

All statistical analysis will be carried out by the professionals using the SPSS (version 22.0) software. The statistical analysts will be unclear about the specific grouping content of the trial. In the present study, we will use a full analysis set (FAS) and per-protocol set (PPS), and the final conclusion will be based on the results of FAS. The full analysis set (FAS) is based on therapeutic intent. Patients who participate in the randomization but only have received 1-time treatment will also be included in the analysis. In the FAS analysis, for patients who do not complete the trial, the main indicators missed will be derived from the last observation carried forward (LOCF). All statistical analysis will be performed by bilateral differential test, with a *P* value < 0.05 considered statistically significant. Continuous variables will be presented as mean ± standard deviation (normally distributed data) or medians and ranges (non-normally distributed data). For the balance of basic values, analysis of variance or chi-square test or rank sum test will be used. For the primary and secondary outcomes, the analysis of variance will be used. If confounding factors may have an impact on the results, then the co-variance analysis will be used. Further, we will repeat measurements of the same outcome index of the same group at different time points. Changes involved in the rates before and after treatment in each group will be measured by the chi-square test or non-parametric test. The paired *t* test will be used to compare the differences between the groups before and after treatment.

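### The unadjusted all-patient analysis of variance suits NRS ear pain poorly: perhaps a third of patients may start at 0, so the pain effect is diluted and precision is lost

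*Protocol article*

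**What the plan says.** The NRS section defines a 0 to 10 pain scale on which "0 means no pain, 10 means severe pain which is unbearable". It places the assessments at two times: "The measurements will be performed within the baseline and day 10 after onset". (Table 1 also marks NRS at day 30.)

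The Discussion explains that the scale is meant for pain behind or around the ear. It concedes that pain is not universal, "although this symptom did not observe in all the patients", and then cites an early epidemiological survey in which "the incidence of pain behind or around the ear is 63" per cent. It concludes: "Therefore, we conducted a statistical analysis and analyzed the degree and duration of pain".

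Neither the inclusion nor the exclusion criteria mention pain.

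The Statistical analysis section gives one rule for all outcomes: "For the primary and secondary outcomes, the analysis of variance will be used". Adjustment is conditional and no covariate is named: "If confounding factors may have an impact on the results, then the co-variance analysis will be used". Conclusions rest on the full analysis set (FAS). No exception is made for NRS.

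**The concern.** A patient who enters with NRS 0 has no pain to relieve; the score can only stay at 0 or rise. If such patients are a sizeable share, an unadjusted all-patient mean comparison does two things. It averages the effect in patients with pain with a group in which relief is impossible, so the estimated difference shrinks. It also mixes patients near zero change with patients who change a lot, so the spread grows. Both reduce the chance of detecting pain relief if it exists.

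The result also becomes harder to read, because relief of existing pain and onset of new pain fall into one mean. That matters somewhat here. Safety is a stated aim, and the rationale for the design reports a worry that acute-phase electroacupuncture may aggravate nerve edema.

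This is not mere silence in a condensed article. The authors knew that the symptom is not universal and still fixed one general method for every secondary outcome.

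**Working it through.** **Plan's own figures.** The protocol gives no effect size, SD or power for NRS. The only sample size is for the Sunnybrook score: 36 per group, 40 after a 10% allowance. It reproduces with a difference of 38.3 − 32.3 = 6, SD 8.1, two-sided alpha 0.025 and 80% power: (2.241 + 0.842)² × 2 × 8.1² / 6² = 34.6, so 35; the t-based version gives 35.9, so 36; and 36 / 0.9 = 40. I therefore use 40 per arm.

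**Share at the floor.** If the survey figure applied at baseline, 100% − 63% = 37% would start at 0. Per arm that is 0.37 × 40 = 14.8 without pain and 0.63 × 40 = 25.2 with pain, or about 30 and 50 of 80.

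**Model (assumed).** Pain-free patients stay at 0. In patients with pain, the control arm improves by m points, the experimental arm by m + d, and the SD of change is s.

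- All-patient difference: 0.63 × d.
- Variance per arm: 0.63 × s² + 0.63 × 0.37 × (m + d/2)², where m + d/2 is the mean improvement averaged over the two arms.
- All patients: z = 0.63 d / √(2 × variance / 40).
- Patients with pain only: z = d / √(2 s² / 25.2).
- Power = Φ(z − 1.96), two-sided 5%.

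**Example, d = 1, s = 2.**

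- Pain only: z = 1 / √(8 / 25.2) = 1.775; power 43%.
- All patients, m = 0: variance = 2.52 + 0.2331 × 0.25 = 2.578; z = 0.63 / 0.359 = 1.755; power 42%.
- All patients, m = 3: variance = 2.52 + 0.2331 × 12.25 = 5.376; z = 0.63 / 0.518 = 1.215; power 23%.

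**Range, s = 2 (power, all patients).**

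| d | m = 0 | m = 1 | m = 2 | m = 3 | m = 4 | Pain only |
|---|---|---|---|---|---|---|
| 1 | 42% | 37% | 29% | 23% | 18% | 43% |
| 1.5 | 74% | 65% | 53% | 42% | 33% | 76% |
| 2 | 92% | 86% | 75% | 62% | 50% | 94% |

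Using a separate variance in each arm lowers the all-patient figures by at most about 2 points. At a less favourable corner (d = 1, s = 2.5, m = 4) the figures are 16% and 29%.

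**Does baseline adjustment help?** I simulated scores rounded and bounded at 0 and 10, with assumed baseline mean 4.5 and SD 1.8 in patients with pain, control improvement 2, SD 2, and no new pain in the others (3,000 trials per row):

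| d | Change, all | Change, pain only | Baseline-adjusted, all | Baseline-adjusted, pain only |
|---|---|---|---|---|
| 1 | 23% | 34% | 34% | 35% |
| 1.5 | 41% | 61% | 61% | 64% |
| 2 | 58% | 83% | 83% | 85% |

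Under these assumptions, adjusting for baseline NRS in all 80 patients recovers almost all the lost power. It does not change the dilution of the average effect.

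**The case against.** Several points on the other side stand.

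- **The comparison is sound.** Comparing all randomised patients is an unbiased estimate of the average effect on pain in this population. A smaller average is a different question, not an error. A reader might infer that the NRS result would be invalid; the documents do not support that.
- **63% is a survey incidence.** It is not the expected share with pain at enrolment within 3 days of onset. A patient without pain at entry may develop it by day 10, and if treatment prevents that, the patient is informative. The figure of 15 per arm is plausible but assumed.
- **The loss may be small.** It nearly vanishes if control pain barely improves. That is an unlikely planning case, since both arms receive a steroid and the protocol calls the disease self-limiting, but it cannot be excluded.
- **New pain is not hidden.** A reader might infer that needling pain would vanish into the mean. Table 1 schedules adverse-event collection at enrolment and on days 4, 10 and 30, and the adverse-events section requires symptoms and their relation to acupuncture to be recorded.
- **Neither the NRS variable nor an NRS-specific population is named.** The protocol does not say that change is analysed, and duration of pain has meaning only in patients who have it. Such detail often sits in an analysis plan.

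The last point does not remove the concern. The stated rule covers all secondary outcomes and makes no exception. Analysing the unadjusted day-10 score instead of change does not help either: in a further simulation with a floor (assumed baseline mean 5, control improvement 3, difference 1, SD 2) both had 18% power in all patients, against 31% for change in patients with pain. Covariance analysis would help, but the text allows it only if confounding is suspected and does not name baseline NRS.

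**Conclusion.** The point holds as a matter of efficiency and interpretation, not validity. The stated rule sends a pain scale with a floor at 0 through an unadjusted all-patient analysis, although the protocol itself expects many patients to have no pain. If 63% have pain at baseline and the rest stay at 0, the mean difference is about 0.63 of the effect in patients with pain. The accompanying power loss ranges from negligible to large: 42% against 43%, or 23% against 43%, at a difference of 1 and SD 2, depending on whether control pain improves by 0 or 3 points. All NRS inputs other than the 63% are assumptions. Restricting to patients with pain is not the only remedy, since baseline adjustment recovers most of the power when little new pain arises. NRS is a secondary outcome without its own power calculation; the primary Sunnybrook analysis and the sample size are untouched.

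**What to change.** In the NRS and Statistical analysis sections, state that:

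1. Day-10 NRS is compared between arms in all FAS patients by analysis of covariance, with baseline NRS as a fixed covariate and not one added only if confounding is suspected.
2. The comparison in patients with baseline NRS of 1 or more is pre-specified as the estimate of pain relief. Baseline NRS is an enrolment measurement, so this comparison stays randomised provided that the score is recorded before the envelope is opened.
3. New pain (NRS 0 at baseline, 1 or more later) is counted by arm and shown alongside the adverse-event record.

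The same edit should reconcile the NRS section with Table 1 on the day-30 assessment.

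The cost is wording; the data are already collected. The downside is that the pain-relief comparison would use about 50 of 80 patients, answers a narrower question than the all-patient one, and could still have low power (43% at a difference of 1 and SD 2).

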### Trial status

Protocol version number and date: V1.1, dated 14 February 2021. The first participant was enrolled on 28 September 2020. Recruitment will be completed on 30 April 2021.

## Data Availability

The datasets generated and/or analyzed are available from the corresponding author upon reasonable request.

## Abbreviations

IFP: Idiopathic facial palsy
SFGS: Sunnybrook (Toronto) Facial Grading System
H-B: House-Brackmann Facial Nerve Grading System
NRS: Numerical Rating Scale
FDI: Facial Disability Index scale
sEMG: Surface electromyogram
MRI: Magnetic resonance imaging
FP: Facial palsy
FND: Facial nerve decompression
SAE: Serious adverse event
FAS: Full analysis set
PPS: Per-protocol set
LOCF: Last observation carried forward
SOP: Standard operation procedure
ACTH: Adrenocorticotrophic hormone
